#### 15. ENDPOINTS (This section has been amended. Please refer to the information in “Amendment” section.)

##### 15.1 Primary Endpoints

- (1) Change from month baseline at month 36 in femoral neck BMD;
- (2) Change from month baseline at month 36 in lean mass of left thigh;
- (3) Change from month baseline at month 36 in TUG test;
- (4) The number of falls during the 36 months.

## 15.2 Secondary Endpoints

- (1) Change from month baseline at month 36 in osteocalcin;
- (2) Change from month baseline at month 36 in deoxypyridinoline;
- (3) Changes from baseline at month 36 in estradiol;
- (4) Change from month baseline at month 36 in endometrial thickness;
- (5) Nature, frequency and severity of adverse events and their relationship to treatment.

We will also assess vital signs, laboratory values and electrocardiographic variables during the 36-month follow-up.

## 16. STATISTICAL CONSIDERATIONS (This section has been amended. Please refer to the information in “Amendment” section.)

### 16.1 Data Collection Forms

Patient information collected for the trial is recorded on the appropriate CRFs. All completed CRFs must be submitted to the sponsor at the end of month 36.

### 16.2 Data Management

After confirming the correct database established by PI, the pre-defined analysis plan in the study should be finalized before database lock and unblinding. Under the supervision of the trial project manager, a data management system will be administered. The data management system for the trial is in-built. The inspector will monitor enrollment, loss to follow up, adherence and satisfaction with intervention, as well as adverse events. These regulations that ensure complete patient and data safety and confidentiality will be instituted and documented meticulously.

### 16.3 Statistical Analysis

All the analyses will use randomly assigned patients under ITT principle. For patients missing data, the LOCF approach use to analyze the longitudinal data. Repeated-measures ANOVA analysis should be carried out between two groups and four times (baseline, 12, 24 and 36 months). Within-subjects results will be used *t*-test on the percentage change from the baseline value. The

numbers of falls and adverse events will perform by chi-square test. All tests will be used two-sided and set at the 5% level.

## **17. QUALITY ASSURANCE**

### **17.1 Training**

The study will be conducted in accordance with GCP and with all relevant regulations. All research staff will be trained on the study protocol and procedure manuals before the start of participant recruitment. All required study information must be recorded on medical documents or CRFs. Study data derived from laboratories and subject follow-up visits, clinic attendance, and screening will all be collected with corrective actions executed as required throughout the duration of the study.

### **17.2 Diet and Exercise Control**

During the entire trial, the subjects will be advised to follow the guideline for daily dietary intake and physical activities, such as intaking high-protein diet, avoiding alcohol abuse and smoking, and keeping active in daily physical activities. The questionnaire for daily dietary intake and physical activities (DDIPA; Appendix F) should be recorded at 12, 24, 36 months during 36-month clinical trial. Calcium and vitamin D supplement on their own should be prohibited in 36-month clinical trial.

### **17.3 Data Quality**

The PI will inspect an on-site study that contain the study protocol, manual of procedures, informed consent form, IRB document, medication records, general trial correspondence and patient screening logs for reference. The PI is responsible for ensuring regular submission of the completed CRFs in monitoring and analysis. In the event of incomplete, incongruous or ambiguous data, the investigator and/or coordinator will be contacted for clarification. The PI is responsible for data accuracy, consistency and quality.

CRFs and biological samples will be labeled with a unique study identifier. Ten percent of CRFs will be duplicated and the copy will be used for double data entry. All quantitative data will be entered into a Microsoft Excel and audited for accuracy. Coded forms will be kept separately from the code list to maintain confidentiality information. All forms will be stored in locked file

cabinets or desks in a locked office.

All worksheets, documents and administrative records should be retained by the investigator. The investigator should refer to the associated procedures manual for further information regarding details of the procedures to be followed during the course of the trial.

#### 17.4 Monitoring

The purpose of visits will be to ensure that the study is conducted according to the protocol and GCP guidelines. These quality control reviews will also inspect study records and source documents for specific verification of participant details, data quality, and completeness of intervention implementation.

Access to CRF, source documents, and other study files must be made available at two sites for monitoring and audit purposes at these monitoring visits during the course of the study and after the study. Any deviations will be documented.

#### 17.5 Interim Analysis and Stopping Guidelines

An interim analysis will be performed at month 12. Although this is a 3 year study, the primary analysis will occur after all subjects have had the opportunity to complete the month 12 study visit. In order to maintain the blind, study staff at the Office of Scientific Research and Teaching who have direct contact with the sites will have access to results from the interim and primary analyses only at aggregate level until all subjects have completed the study and the treatment assignments have been unblinded. The month 36 data will be analyzed separately at the end of the study.

The study staff at the Office of Scientific Research and Teaching will review the safety and efficacy data for BSYJF/placebo. If at any time there are safety concerns, the study staff will communicate the concerns with a coordinator. The start date will depend on the subject's accrual enrollment.

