#### With:

#### **Primary endpoint:**

**Primary endpoint is the number of falls at 36 months.**

## Section: 15.2 Secondary Endpoints

Replace:

- (1) Change from month baseline at month 36 in osteocalcin;
- (2) Change from month baseline at month 36 in deoxypyridinoline;
- (3) Changes from baseline at month 36 in estradiol;
- (4) Change from month baseline at month 36 in endometrial thickness;
- (5) Nature, frequency and severity of adverse events and their relationship to treatment.

With:

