| Endpoints                  | 
Endpoints are to be evaluated for BSYJF versus placebo.
 
Primary endpoint:
 
 
1. Number of falls at month 36.
 
 
Secondary endpoints:
 
 
1. Change from month baseline at month 36 in femoral neck BMD;
 
2. Change from month baseline at month 36 in lean mass of left thigh;
 
3. Change from month baseline at month 36 in TUG test;
 
4. Change from month baseline at month 36 in biomarkers of bone turnover (osteocalcin and deoxypyridinoline).
 
5. Change from month baseline at month 36 in endometrial thickness;
 
6. Change from month baseline at month 36 in estradiol;
 
7. Nature, frequency and severity of adverse events and their relationship to treatment.
 
 
Additional endpoint:
 
8. Number of falls at the end of 10 years extension follow-up.
 |
| Statistical considerations | 
All the analyses will use all randomly assigned patients under ITT principle. For patients missing data after the baseline, the LOCF approach use to analyze the longitudinal data. The number of falls at month 36 and adverse events will perform by chi-square test. Kaplan–Meier analysis will be calculated in order to demonstrate differences in number of fallers over time. The time to first fall will be analyzed using a Cox regression
                                                                                                                                                                                                                                                                                                                                                                                                                                                                                                                 |

|  |                                                                                                                                                                                                                                                                                                                                                                                                                                                                                                    |

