|--|----------------------------------------------------------------------------------------------------------------------------------------------------------------------------------------------------------------------------------------------------------------------------------------------------------------------------------------------------------------------------------------------------------------------------------------------------------------------------------------------------|
|  | 
analysis providing a 95% confidence interval. Repeated-measures ANOVA analysis should be carried out between two groups and four times (baseline, 12, 24 and 36 months). Within-subjects results will be used t-test on the mean percentage change from the baseline value. All tests will be used two-sided and set at the 5% level.
 
Additional analysis:
Number of falls at the end of 10 years extension follow-up will be performed by chi-square test.
 |
|--|----------------------------------------------------------------------------------------------------------------------------------------------------------------------------------------------------------------------------------------------------------------------------------------------------------------------------------------------------------------------------------------------------------------------------------------------------------------------------------------------------|

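### Section 17.5 places the primary analysis at month 12, but the only primary endpoint is falls at month 36, so the protocol names two different primary analyses

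*Supplement*

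**What the plan says.** Section 17.5 (Interim Analysis and Stopping Guidelines) makes four statements that bear on this point:

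- "An interim analysis will be performed at month 12".
- Although the study lasts three years, "the primary analysis will occur after all subjects have had the opportunity to complete the month 12 study visit".
- "The month 36 data will be analyzed separately at the end of the study".
- Staff of the research office "will review the safety and efficacy data for BSYJF/placebo".

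The endpoint text points elsewhere. Amendment 1 makes falls the only primary endpoint, and its replacement for section 15.1 reads "Primary endpoint is the number of falls at 36 months". The synopsis in Amendment 2 (version 1.2) repeats it as "Number of falls at month 36" and attaches the test to that time: "The number of falls at month 36 and adverse events will perform by chi-square test". The same synopsis gives the only rule on error rates: "All tests will be used two-sided and set at the 5% level".

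Amendment 1 changes the synopsis and sections 11, 12 (Table 1), 12.3, 15.1, 15.2 and 16.3. Amendment 2 changes the synopsis and sections 3.3, 5.1, 6.2, 9, 12 (Table 1), 15.2 and 17.2. Neither lists section 17.5, so it stands as first written.

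**The concern.** An analysis triggered by the month-12 visit cannot analyse an endpoint measured at month 36. Read literally, section 17.5 makes one year of falls decisive and treats the three-year data as a separate exercise. The endpoint and statistics sections say the reverse.

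Two things are at stake. First, which analysis decides the trial has to be settled before data are seen. With the text as it is, either a month-12 or a month-36 result could be called the protocol's primary result. Second, if both times carry a between-group test at the blanket 5% level and either can count as success, the chance of a false positive exceeds 5%. If month 12 really were primary, the trial would also rest on far fewer falls than three years would supply.

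**Working it through.** **1. The two statements side by side**

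| Place | What is primary | When |
|---|---|---|
| Section 17.5 | the primary analysis | once all women could have completed month 12 |
| Amendment 1, replacement for 15.1 | number of falls | 36 months |
| Amendment 2 synopsis | number of falls, chi-square | month 36 |

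No sentence reconciles the first row with the other two. The original section 15.1 also placed its primary endpoints at month 36, so section 17.5 did not match the endpoints before the amendments either.

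**2. Overall type I error if both times are tested**

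Inputs: two-sided 5% at each look (Amendment 2 synopsis, applied to both looks by inference). The information fraction t at month 12 is not in the documents. I assume t = 1/3 (12 of 36 months) and show a range of 0.2 to 0.5.

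Under no effect, the two z-statistics are taken as bivariate normal with correlation √t. Overall error = 1 − P(|Z₁| < 1.96 and |Z₂| < 1.96).

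| t | √t | P(neither significant) | Overall error |
|---|---|---|---|
| 0.2 | 0.447 | 0.908 | 9.2% |
| 1/3 | 0.577 | 0.912 | 8.8% |
| 0.5 | 0.707 | 0.917 | 8.3% |

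Independent looks would give 1 − 0.95² = 9.75%. A single confirmatory test at month 36 gives 5%.

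**3. Power if month 12 were the primary test**

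Inputs from section 11: 19% fallers on placebo, a 50% reduction described as annual, 55 per group (70 recruited), and a target of 90% power at one-sided 5%. I assume that 19% is a 12-month incidence, so the comparison is 19% against 9.5%.

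The plan's own figure comes first. With the pooled two-proportion formula, those rates at one-sided 5% and 90% power need 231 per group, not 55. The stated figure does not reproduce on this reading.

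Power = Φ{[Δ√n − z√(2p̄(1−p̄))] / √(p₁(1−p₁) + p₂(1−p₂))}, with Δ = 0.095 and p̄ = 0.1425. The two square roots are √0.2444 = 0.4944 and √0.2399 = 0.4898.

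- n = 55, two-sided: (0.7045 − 1.96 × 0.4944)/0.4898 = −0.54, power 29%.
- n = 55, one-sided: (0.7045 − 1.645 × 0.4944)/0.4898 = −0.22, power 41%.
- n = 70: 36% two-sided, 49% one-sided.

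For comparison, compound the same annual rates over three years: 1 − 0.81³ = 46.9% and 1 − 0.905³ = 25.9%. With 55 per group the month-36 power is 63% two-sided or 74% one-sided, which is also below 90%.

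**4. Boundaries if a month-12 efficacy test is kept (t = 1/3)**

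O'Brien-Fleming-type spending depends on the convention:

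- Spending 0.025 on each side: 2 × 2{1 − Φ(2.241/0.577)} = 0.0002 two-sided at month 12, leaving 0.0499 at month 36.
- Spending 0.05 directly: 2{1 − Φ(1.960/0.577)} = 0.0007 at month 12, leaving 0.0497 at month 36.

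**The case against.** The strongest reply is that month 36 is clearly meant. Amendment 1 makes falls the only primary endpoint, version 1.2 ties the chi-square test to month 36, and section 17.5 is a leftover paragraph. That is a fair guess at intent. It does not remove the conflict, because section 17.5 is still in force and its remark about the three-year length suggests that the month-12 timing was deliberate.

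A reader might infer that the plan sets an unadjusted 5% test at both looks and so has an inflated error rate. The documents do not go that far. No sentence gives a test, a significance level or a success criterion for month 12. The 5% rule is a blanket one that does not mention the interim look. Section 17.5 limits site-facing staff to aggregate results, and the only action it describes is passing on safety concerns. The inflation is therefore conditional.

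The missing boundary is also not a fault in itself. Section 16.2 foresees an analysis plan finalised before database lock, that plan is not shown, and boundaries are often placed there. The contradiction inside the protocol does not depend on it.

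Finally, a reader might set 29% power against the promised 90% and blame the whole gap on the month-12 timing. That overstates it. The 29% is two-sided and uses 55 per group, while the 90% target is one-sided. Under intention to treat all 70 per group would count, and the 19% is not plainly stated to be a 12-month rate. On the same reading the month-36 test also misses 90%, so part of the gap is a separate sample-size problem.

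**Conclusion.** The contradiction is certain: the current protocol names two different primary analyses, one at month 12 and one at month 36. It needs no assumption beyond the text, and it must be fixed.

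The error-rate consequence is conditional. If falls are tested between groups at both times and either result counts, type I error is about 8.8% in place of 5%, with the information fraction of 1/3 assumed. If month 12 is descriptive or safety-only there is no inflation, and what remains is a wrong label.

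The power consequence applies only if month 12 is really primary and 19% is an annual incidence. Power would then be about 29% to 36% two-sided, or 41% to 49% one-sided, with 55 to 70 per group.

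**What to change.** Rewrite section 17.5 to say that the single primary analysis is falls through month 36, done after the last participant's month-36 visit, and that month 12 is a safety review with no confirmatory efficacy test.

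If the sponsor wants an efficacy test at month 12, pre-specify an alpha-spending boundary and name the convention. One option among several is O'Brien-Fleming-type spending at one third of the information: two-sided p of about 0.0002 (0.025 spent per side) or about 0.0007 (0.05 spent directly). Either leaves the month-36 test at essentially 5%.

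The cost is one paragraph, with no extra participants or visits. The sponsor gives up a month-12 efficacy claim that the endpoint sections do not support. The sample-size question needs its own correction.

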### **18. PARTICIPANTS' RIGHTS AND CONFIDENTIALITY**

#### 18.1 Institutional Review Board

This protocol, ICF and any subsequent modifications will be reviewed and approved by IRB for written approval, which is responsible for oversight of

the study. The investigator should notify the IRB of deviations from the protocol or SAE occurring at the site. The study may be discontinued at any time by the IRB as part of their duty to ensure that participants are protected.

### 18.2 Subject Confidentiality

CRFs will be stored in locked cabinets at participating clinics and will be accessed only by permitted study staff and the monitor from the Office of Scientific Research and Teaching. Names and other easily recognizable identifiers will be removed from CRFs prior to data entry and analysis. Instead, identification numbers will be used so that data and specimens may be linked; these are not meaningful to casual observers without access to the original study logs. Any data, specimens, forms, reports, and recordings that leave the site will be identified only by the identification number to maintain confidentiality.

The study records will be available to regulatory agencies, such as IRB. All trial staff will be trained in procedures to minimize the potential breaches of confidentiality, including but not limited to, ensuring that all files are closed and no conversations about individual participants occur in public.

### 18.3 Conflict of Interests

The sponsor has established a policy regarding Conflict of Interests to be adhered to by investigators. The policy will provide rules to conduct the trial in an unbiased and informed manner that meets public standards.

## 19. PUBLICATION POLICY

To coordinate dissemination of data from this study, data will be reviewed for validity and subsequent publication. The investigators will develop a suitable policy protecting the rights regarding ownership of study materials and data. Briefly, manuscripts will be in the name of appliances; the supporters will be acknowledged. Each author should have participated sufficiently in the work to take public responsibility for appropriate portions of the content.

## 20. FUNDING

This trial is funded Ministry of Science & Technology of China (Project No.

96-906-09-05), and Shanghai Science & Technology Commission (Project No. 004319226).

### Appendix C. Falls Recording Form

| Record No.
of each fall | Date
(yy-mm-dd) | Perceived Causes                                                                                                                                                       | Body site to
touch ground                                                                                                           | Injury                                                                                                                     | Fracture                                                                                                                                      |
|----------------------------|--------------------|------------------------------------------------------------------------------------------------------------------------------------------------------------------------|----------------------------------------------------------------------------------------------------------------------------------------|----------------------------------------------------------------------------------------------------------------------------|-----------------------------------------------------------------------------------------------------------------------------------------------|
| 1                          |                    |  Balance/gait impairment
 Dizziness/vertigo
 Accident
 Others |  Wrist
 Shoulder
 Hip
 Others |  No injury
 Untreated injury
 Treated injury |  No fracture
 Vertebral
 Hip
 Others |
| 2                          |                    |  Balance/gait impairment
 Dizziness/vertigo
 Accident
 Others |  Wrist
 Shoulder
 Hip
 Others |  No injury
 Untreated injury
 Treated injury |  No fracture
 Vertebral
 Hip
 Others |
| 3                          |                    |  Balance/gait impairment
 Dizziness/vertigo
 Accident
 Others |  Wrist
 Shoulder
 Hip
 Others |  No injury
 Untreated injury
 Treated injury |  No fracture
 Vertebral
 Hip
 Others |
| 4                          |                    |  Balance/gait impairment
 Dizziness/vertigo
 Accident
 Others |  Wrist
 Shoulder
 Hip
 Others |  No injury
 Untreated injury
 Treated injury |  No fracture
 Vertebral
 Hip
 Others |
| 5                          |                    |  Balance/gait impairment
 Dizziness/vertigo
 Accident
 Others |  Wrist
 Shoulder
 Hip
 Others |  No injury
 Untreated injury
 Treated injury |  No fracture
 Vertebral
 Hip
 Others |

**Note:** A fall is defined as any event that led to an unplanned, unexpected contact with a supporting surface.

**Appendix D. Timed Up and Go (TUG) test**

The TUG test is designed to evaluate the functional mobility of the participants. Subjects observe and time from the instant they rising from an armchair, walking to a mark 3 meters away, turning around and returning to sit back in the chair at a regular pace. Subjects wear their usual footwear and allow using the arms of the chair to get up. Subjects begin the test on the word, “go” and are instructed to “walk”. Each subject performs TUG test 3 times and the fastest of these tests is finally recorded in seconds. A practice trial uses to test each subject understanding. Same chair is used for re-testing during the trial.

